## Abstract

**Background:**

Cognitive behavior therapy (CBT) is the first-line of treatment for overweight and obesity patients whose problems originate in maladaptive eating habits (e.g., emotional eating). However, in-person CBT is currently difficult to access by large segments of the population. The proposed SIGMA intervention (i.e., the Self-help, Integrated, and Gamified Mobile-phone Application) is a mHealth intervention based on CBT principles. It specifically targets overweight young adults with underlying maladaptive behaviors and cognitions regarding food. The SIGMA app was designed as a serious game and intended to work as a standalone app for weight maintenance or alongside a calorie-restrictive diet for weight loss. It uses a complex and novel scoring system that allows points earned within the game to be supplemented by points earned during outdoor activities with the help of an embedded pedometer.

**Methods/design:**

The efficacy of the SIGMA mHealth intervention will be investigated within a randomized, placebo-controlled trial. The intervention will be set to last 2 months with a 3-month follow-up. Selected participants will be young overweight adults with non-clinical maladaptive eating habits embodied by food cravings, binge eating, and emotional eating. The primary outcomes will be represented by changes in (1) self-reported maladaptive thoughts related to eating and body weight, (2) self-reported maladaptive eating behaviors in the range of urgent food cravings, emotional eating or binge eating, (3) as well as biased attentional processing of food items as indexed by reaction times. Secondary outcomes will be represented by changes in weight, Body Mass Index, general mood, and physical activity as indexed by the number of steps per day.

**Discussion:**

Through an evidence-based cognitive behavioral approach and a user-friendly game interface, the SIGMA intervention offers a significant contribution to the development of a cost-effective and preventive self-help tool for young overweight adults with maladaptive eating habits.

**Trial registration:**

ISRCTN, ID: 70907354. Registered on 6 February 2017. The ISRCTN registration is in line with the World Health Organization Trial Registration Data Set. The present paper represents the original version of the protocol. Any changes to the protocol will be communicated to ISRCTN.

**Electronic supplementary material:**

The online version of this article (doi:10.1186/s13063-017-2340-6) contains supplementary material, which is available to authorized users.

## Background

Obesity, commonly characterized by a Body mass Index (BMI) equal to or exceeding 30 kg/m^2^, has become a worldwide health issue with consequences such as morbidity, disability, chronic diseases, and emotional health problems associated with weight stigma [1, 2]. Currently, obesity and overweight affect as many as 30% of the worldwide population and this number is expected to grow up to 50% by 2030 [3]. The high rates of obesity and their aforementioned health consequences strain the public health system and result in significant economic and societal burden [4]. This highlights an urgent need for readily accessible evidence-based interventions aimed at prompting weight loss and weight maintenance.

Currently, CBT is the first-line of treatment for overweight and obesity cases that originate in *maladaptive eating habits* (i.e., eating in the absence of hunger, eating prompted by stress or negative emotionality) [5, 6]. Maladaptive eating habits are the main cause behind “yo-yo” dieting and represent a barrier to losing weight and to a healthy lifestyle [7], as well as an important relapse factor after bariatric surgery [8].

CBT targets not only (1) maladaptive behavioral habits, but also (2) *maladaptive cognitive styles* (e.g., dysfunctional or unhealthy beliefs). Maladaptive cognitive styles are central in CBT and are theorized to underlie negative emotions and undesirable behaviors, such as emotional eating, as indicated by several trials [9, 10] and reviews (e.g., [11]).

Maladaptive behaviors and cognitive styles can be best assessed and altered in their ecological environment. A potential avenue towards achieving this is the delivery of interventions through smartphone apps (i.e., mHealth interventions). These interventions are particularly relevant for the young adult population (i.e., 18 to 35 years old) for two main reasons. Firstly, young adults (i.e., 18 to 35 years old) are particularly susceptible to becoming overweight or obese (e.g., [12]). Moreover, weight gain during this life-stage is not only a marker of obesity but also for developing chronic disease risk factors (e.g., high blood pressure; [13]). Secondly, young adults are the most likely age group to own and constantly interact with smartphones. As many as 100% of young adults in developed countries own smartphones, with constantly increasing rates in developing countries as well [14, 15]. Therefore, the increased usage of mobile phones among the young adult population and the health consequences associated with early-life weight gain provide the motivation for delivering weight management interventions (i.e., mHealth) on a large scale and in an ecological manner.

Mobile or mHealth interventions for weight management have demonstrated promising results across various studies [16]. However, they face two important limitations, as argued below.

The first limitation is that most studies report up to a 50% dropout rate in the use of existing mHealth and eHealth applications (i.e., electronic/technologically mediated apps), which makes them subject to short-term use only [17]. A potential solution for long-term use would be to increase the interactivity and attraction of current mHealth interventions via gamification. Gamification refers to the employment of game-like components (e.g., challenges, storylines) in non-game contexts such as psychological interventions [18]. Although research on the topic remains in its initial stages, current evidence suggests that gamification can have a positive impact on motivation and health behaviors [19] and, most importantly, it promotes long-term treatment adherence [18, 20, 21].

A second limitation of existing m/eHealth interventions is that currently there is no available application or scientific trial targeting maladaptive eating habits despite their high prevalence in overweight individuals [22]. Hence, new portable, evidence-based, integrated, and interactive applications for weight management are needed.

Therefore, the purpose of the SIGMA application (i.e., the Self-help, Integrated, and Gamified Mobile-phone Application) is to primarily address the maladaptive behavioral and cognitive styles that impede weight management in young adults at risk for obesity (BMI 25–29.9 kg/m^2^). The SIGMA app is a CBT-based intervention that was designed as a serious game and is intended to work as a standalone app for weight maintenance or alongside a calorie-restrictive diet for weight loss. The aim of this report is to describe the theoretical rationale and intervention design of the SIGMA study.

### Theoretical framework

The SIGMA intervention was informed by CBT’s *cognitive ABC model* (*A*ntecedents – *B*eliefs – *C*onsequences). The cognitive ABC model states that negative emotions and undesirable eating behaviors (C) are caused and maintained, contrary to common beliefs, not by adversities or antecedents (A), but by (1) maladaptive beliefs and (2) faulty information processing (B) [23] concerning those adversities, as evidenced below.Maladaptive beliefs are central in CBT for obesity. Prior research has indicated that obese participants have more unhealthy food and weight-related beliefs including catastrophizing, faulty body-image perception, and poor self-control than healthy-weight participants [24–26]. According to CBT’s ABC model, maladaptive beliefs (B), particularly sabotaging thoughts, cause uncontrolled and unplanned eating (C). Osberg, Poland, Aguayo, and MacDougall ([27], p.26) define sabotaging thoughts as “cognitively distorted and unhealthy attitudes and beliefs regarding food” (e.g., I can’t possibly live without chocolate).An example of the cognitive ABC model is the following: (A) a feeling of sadness in the context of losing a job triggers a sabotaging thought (B) – “I hate this feeling. If I eat I will feel better” that causes (C) emotional eating followed by guilt (A) and the loop of maladaptive cognitive and behavioral styles is preserved. Hence, CBT’s *mechanism of change* is not A, nor C, but B. In other words, the aim of CBT is to replace maladaptive beliefs with more adaptive and healthy alternatives (e.g., “I don’t like this feeling, but eating won’t solve my problem”) that help adherence to a calorie-restricted diet and prevent gaining any additional weight [28]Another central factor in the CBT conceptualization of obesity refers to faulty information processing, a selective processing of food stimuli in the environment. One highly investigated faulty information process is attention bias to food cues, otherwise known as the tendency to attend to food stimuli. A growing body of research has indicated that biased attention toward food predicts the strength of cravings [29], stress eating [30], the amount eaten, and even the amount of weight gained in obesity cases [31, 32]

Attention bias is theorized to precede maladaptive beliefs, making environmental stimuli more difficult to resist [33]. Targeting attention biases is a complementary path that maximizes resistance to tempting situations which become less likely to trigger sabotaging thoughts. This process operates at an implicit level, but there is evidence that it can be modified by specific interventions (i.e., ABM – attention bias modification; [34]) that can be successfully integrated into CBT [35].

Overall, the ABC model provides an evidence-based theoretical guiding structure for the SIGMA intervention.

## Methods/design

The SIGMA trial will be a randomized, placebo-controlled trial designed to last for a total of 22 weeks including a 2-week baseline point. The randomization procedure is described in detail in the “Randomization and blinding” section. The primary objective of this trial is to contrast the SIGMA intervention against a sham intervention that will include all the modules developed for the SIGMA intervention with the exception of the gamified intervention module. Therefore, it will lack the active/distinctive features of the SIGMA app.

The Standard Protocol Items Recommendations for Interventional Trials (SPIRIT) Statement 2013 are followed (see also Additional file 1: SPIRIT 2013 Checklist: recommended items to address in a clinical trial protocol and related documents). The trial was registered under the registration number ISRCTN70907354 on 6 February 2017.

### Intervention design

The SIGMA intervention is designed to accommodate four mHealth modules, which will be further described in the following paragraphs and are depicted in Fig. 1. For the purposes of the SIGMA trial, all participants (both intervention and control groups) will be asked to actively follow a calorie-restrictive diet of their own choice. General information about dieting and daily exercising is embedded in the psycho-education module of the SIGMA app and should assist in choosing a healthy and balanced calorie-restrictive diet. This information will also be accessible online via the study’s dedicated website if more detailed content is needed.

**Fig. 1 Fig1:**
[figure not shown]
Overview of the Self-help, Integrated, and Gamified Mobile-phone Application (SIGMA) trial configuration

#### The psycho-education module

On opening the app, users are prompted to access the psycho-education module where information about the purpose of the app, as well as information about physical activity and dieting is provided. Users are informed about the etiological role played by maladaptive behavioral and cognitive styles in gaining weight. Other included aspects are the differences between hunger and craving and information on how controlling the environment (e.g., not having tempting food in the house) may be a successful strategy for weight management. Moreover, the psycho-educational content will also be present throughout the app’s usage in the form of daily tips and messages.

#### The gamified intervention module

The gamified intervention module incorporates two sub-modules, namely the explicit cognitive-behavioral intervention and the implicit attention-training intervention, which are described below. The SIGMA modules, especially the intervention module, follow the guidelines of the Beck CBT protocol for weight management [36].

#### The explicit cognitive-behavioral intervention (SIGMAe)

This component of the intervention targets sabotaging thoughts regarding food, as well as maladaptive eating habits (Fig. 2). The gamified interface is an important element of this module, providing (1) a storyline, (2) animated characters that go through difficult and tempting situations, (3) learning opportunities to cope with temptations, and (4) a reward point system that opens new theory-based game levels, as detailed below. The SIGMAe game is inspired by the Beck CBT protocol for weight management [36].

**Fig. 2 Fig2:**
[figure not shown]
Overview of the Self-help, Integrated, and Gamified Mobile-phone Application - explicit cognitive-behavioral intervention (SIGMAe) interface

The storyline is standard; the users learn that they are superheroes in training who should help save the world and the characters from eating temptations. In the game, the characters find themselves in a situation where they should resist temptations, such as eating some highly palatable food, eating when feeling distressed or eating in a social context. To facilitate real-life application, the game-settings are diverse, varying from home-inspired scenarios to holiday and social gathering scenarios. The user’s task is to assist the characters in making a decision in the context of a problematic situation. This will be achieved by choosing the best coping card out of four possible alternatives, varying from the worst coping option to the best coping option (Table 1). These alternatives are organized by levels and can target either behavioral choices, cognitive self-statements or a combination of both (Table 1). Once the user has chosen a coping card, SIGMA will provide *healthy habit points*, which increase the user’s total score and *mastery* level and allow them to further advance in the game. Noteworthy, the app provides feedback, explaining why the chosen coping card is correct or not.

**Table 1 Tab1:** The Self-help, Integrated, and Gamified Mobile-phone Application explicit cognitive-behavioral intervention (SIGMAe) behavioral (B), cognitive (C), and cognitive-behavioral (CB) coping choices exemplified

Worst coping card alternative		Best coping card alternative
Emotional eating scenario: Ann just got separated from her boyfriend. She is sad and in order to help her feel better her friends booked a table at her favorite restaurant. Ann says to herself:		
B	I can hardly wait to go to the restaurant and eat all I can eat to feel better	I know that my favorite restaurant will be a tempting setting for me, especially in these circumstances. I suggest going to bowling
C	It’s terrible what happened to me. There is no way out. My friends are right; we should go out and eat	It is unpleasant what happened to me; however, I can cope with this situation
CB		It is unpleasant what happened to me; however, I can cope with this situation. In addition, there are plenty more things to do than eating my feelings, like go bowling
Binge-eating scenario: Eliza is approaching the fridge. She feels like she is going to lose control. Eliza says to herself:		
B	I can’t help myself. I will eat as much as I want	I will do my relaxation exercises and then I’ll read something
C	It is not fair. Others can eat all they want. Why shouldn’t I?	It may not seem fair; however, eating until I can no longer eat is hardly a solution
CB		It may not seem fair; however, eating until I can no longer eat is hardly a solution. Instead, I will do my relaxation exercises
Craving scenario: when watching TV, Daniel is always tempted to eat a bag of chips or chew something. He says:		
B	I’ll eat chips while watching TV	If I am going to watch TV, I might as well play with my dog
C	I must eat something; I am not used to simply watching TV	No need to eat chips while I watch TV. I can do without
CB		No need to eat chips while I watch TV. I can do without or if not I can play with my dog

The complexity of the explicit intervention will increase as the user interacts with the app and accumulates more points. The tasks at hand provide three levels of difficulty as follows: easy (behavioral), medium (cognitive), and complex (cognitive-behavioral) (Table 1). In order to facilitate learning, previously encountered scenarios at each level will be repeated in a random fashion. The application offers the option of social media sharing as well.

The gamified intervention consists of 300 scenarios including craving, binge, and emotional eating scenarios. In order to ensure a steady progression and involvement, the user will be limited to solving a fixed number of scenarios per week. Given that the intervention protocol is set to extend over 2 months (8 weeks), a number of 37 scenarios per week are to be solved in order for all the behavioral, cognitive, and cognitive-behavioral scenarios to be addressed.

#### The implicit attention-training intervention (SIGMAi)

The implicit component of the gamified intervention is aimed at addressing the biased attention towards appetizing stimuli. Therefore, SIGMAi trains the user’s implicit attentional processes towards healthy food choices, while redirecting them from the unhealthy ones. This intervention is inspired by attention bias modification procedures [37] and has two main levels described below, and graphically depicted in Fig. 3.

**Fig. 3 Fig3:**
[figure not shown]
Overview of the Self-help, Integrated, and Gamified Mobile-phone Application - implicit attention-training intervention (SIGMAi) interface

Within the first level, a minimum of two and a maximum of six food images appear simultaneously on the screen while only one food image represents a healthy choice. Its location on the screen varies randomly with each trial. The participant has to choose the healthy food item as fast as possible while ignoring the unhealthy and possibly more appetizing ones. If no choice is made within 2500 ms, the task moves on to the next trial. The second level of gameplay will present the user with two up to six food items for a short amount of time varying from 700 ms to 1200 ms and depending on the number of images per trial. Once the allocated time has expired, the images will be flipped showing a non-descript reverse side. The user will have to remember the location of the healthy food item and flip the reverse side of the correct image.

As in the case of SIGMAe, in order to assure a steady progression and involvement, the user will be limited to solving a fixed number of trials per week. Overall, the intervention protocol is set to accommodate 975 weekly trials and a total of 7800 trials within the 2 months of the intervention.

The stimuli employed in the attention-training intervention were collected from Food-pics ([38]), a database consisting of standardized images of food stimuli. With each healthy food choice, the user earns one healthy habit point. Hence, due to the design and reward points system, the SIGMAi intervention not only helps the user learn the distinction between healthy and unhealthy food items, but it also makes unhealthy food choices less salient [39]. As in the case of SIGMAe, the results of the game can also be shared on social media and with other users.

#### The Crisis and Relapse prevention module

An important component of SIGMA, previously unaddressed in eHealth interventions, is the presence of a *crisis intervention module*. The need for such a module becomes apparent as relapses in dieting are more likely to occur in moments of crisis (e.g., cravings, a decreased mood) [40, 41]. SIGMA’s crisis intervention module is specifically tailored to address these situations. The features of the crisis module are described below.

#### Motivational messages and coping strategies

The app offers, when requested, written motivational messages or cognitive-behavioral coping strategies, mimicking the coping tips offered by SIGMAe and dependent on the type of encountered issues (e.g., craving, boredom, stress or low mood).

#### Relaxation tools

In the context of emotional eating, particularly for those users who are vulnerable to temptation under stressful conditions, SIGMA’s crisis module will provide guidance in performing relaxing breathing exercises. This is achieved by way of a visual breathing aid. The user can choose between a predefined and a customized breathing rhythm. As a visual aid, an onscreen balloon will expand or contract following the chosen calming breathing pace.

#### Distraction

Because it mimics a standard game (e.g., fast responses to challenges, shifting stimuli) and because it relies on fast and effortlessly responses, the SIGMAi module can also be used for distraction purposes via the crisis module.

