### The SIGMA randomized controlled trial (RCT)

The SIGMA trial is set to be a randomized, placebo-controlled trial that is nationally funded through a research grant. Throughout this trial, the SIGMA intervention will be contrasted against a specific form of placebo, also known as an *attention placebo control condition*. An attention placebo control refers to a condition that mimics an intervention but does not address the proposed mechanisms of change. Participants allocated to the attention placebo control condition will have full access to a modified version of the SIGMA app, which includes all the SIGMA modules except for the gamified intervention module. This control condition is highly suitable to investigate the active ingredients of an intervention, as in our case. Furthermore, this type of control arm is considered a highly valid control condition for RCT’s [46]. Ethical approval for this study was sought and received from the Ethics Committee of the Babeș-Bolyai University (Cluj-Napoca, Romania) and from the Ethics Committee of the University of Bucharest (Bucharest, Romania).

The SIGMA trial will have 2-week calibration point followed by a 2-month intervention and a 3-month follow-up. The schedule of the trial is presented Fig. 4.

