#### Recruitment

Potential participants will be recruited using multiple avenues of communication. Posters describing the intervention and the invitation to take part in the study will be posted in universities around the country. The electronic version of these posters will be distributed around the Internet with a special focus on weight-related forums, Facebook groups, and websites.

Emails describing the purpose of the intervention and an invitation to collaborate will be sent to entities concerned with curbing overweight/obesity rates. These are foundations or associations that are actively engaged in promoting healthy lifestyles by informing the general public about weight-related issues (e.g., Wings Foundation, The Association for Supporting Patients with Obesity, The Romanian Society for the Study of Obesity, etc.).

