#### Constantly monitored aspects

A special feature of the monitoring module is the *ABC diary*. The *ABC diary* is meant to be filled in (1) at the end of the day after an unplanned meal or after an impulsive eating episode took place or (2) in problematic situations, while still contemplating yielding to eating urges. Hence, the *ABC diary* monitoring tool has two features, as detailed below.

When filled in at the end of the day, the *ABC diary* has an awareness role as users can notice what self-reported emotions, cravings, and sabotaging thoughts preceded and ensued their eating behavior. As such, users can choose from a list of emotions, cravings, and beliefs and rate their intensity, or fill in some of their own. An automatically generated graph indicates whether a change in time occurred in any of these variables and pinpoints to triggering/problematic situations.

When filled in problematic situations, the *ABC diary* has a preventive role. In addition to recording emotions, cravings, and sabotaging thoughts, the *ABC diary* monitoring tool provides healthy alternative ways of thinking/coping tips or allows the user to write some personally motivational healthy statements. If alternative ways of thinking do not decrease the urge or desire to eat, then the user is redirected to the Crisis and Relapse prevention module in an effort to reduce the relapse rate.

The healthy habit points system is another constantly monitored aspect. Within the SIGMA application, there are three possible sources of earning points: (1) the explicit cognitive-behavioral intervention (SIGMAe), (b) the implicit attention-training intervention (SIGMAi), and (c) the pedometer. In SIGMAi and SIGMAe awarded points vary from 0 to 8 healthy habit points. Regarding the pedometer, the points received by the user each day will be proportional to the number of steps taken (i.e., 5 points for 5000 steps, 8 points for 8000 steps, etc.). Furthermore, a calorie counter is also available to keep track of daily calorie consumption. However, the application does not encourage a fixation on calorie counting [45]. Hence, no points are earned for its usage. Overall, the points gathered from SIGMAe, SIGMAi, and the pedometer will be assessed separately, as well as pooled into a total score indicative of overall learning and adherence to the intervention.

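### The control app keeps content that works on the protocol's own mechanism of change, so it is not the attention placebo described, and the text leaves open whether controls can reach SIGMAi

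*Protocol article*

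**What the plan says.** All references are to the protocol article.

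- **Definition of the control.** The section on the SIGMA randomized controlled trial describes an attention placebo as "a condition that mimics an intervention but does not address the proposed mechanisms of change". The opening of Methods/design adds that the sham lacks the app's active features.
- **Content of the control.** The same trial section gives controls a modified app "which includes all the SIGMA modules except for the gamified intervention module". Psycho-education, the crisis and relapse prevention module, and the self-monitoring module therefore stay.
- **Mechanism of change.** The Theoretical framework section places it at the B of the ABC model: maladaptive beliefs, which CBT aims to replace with healthier ones. It names attention bias to food as a second factor.
- **Crisis module (retained).** On request it offers "cognitive-behavioral coping strategies, mimicking the coping tips offered by SIGMAe". Under Distraction, "the SIGMAi module can also be used for distraction purposes via the crisis module".
- **ABC diary (retained, in self-monitoring).** The Self-monitoring section says it should help users notice and challenge maladaptive patterns. Under Constantly monitored aspects, in problematic situations it "provides healthy alternative ways of thinking/coping tips", and it sends the user on to the crisis module if the urge persists.
- **Place of SIGMAi.** The section on the gamified intervention module lists SIGMAe and SIGMAi as its two sub-modules.

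**The concern.** The choice of control fixes what the primary contrast can show. If controls receive material that challenges and replaces food-related beliefs, the trial does not set the CBT mechanism against its absence. It sets one way of delivering that mechanism, plus attention training, against a lighter delivery of part of it. A null result on the belief and eating questionnaires could then mean that the mechanism does not work, that both arms received enough of it, or that the game adds nothing to tips and a diary. The protocol's description invites the first reading.

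The SIGMAi route raises a separate issue. Attention bias, measured by a dot-probe task, is one of the three primary outcome domains, and SIGMAi is the component that trains it. If controls can open SIGMAi from the crisis module, they receive the training whose effect that outcome is meant to detect.

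**Working it through.** No arithmetic applies. The check sets the statements side by side.

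**Step 1. Does the retained content act on the stated mechanism?**

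| Requirement or claim | Where | What controls keep | Where |
|---|---|---|---|
| Control does not address the mechanisms of change | The SIGMA randomized controlled trial | Coping strategies modelled on the SIGMAe tips | Motivational messages and coping strategies |
| Mechanism is the replacement of maladaptive beliefs | Theoretical framework | Diary that helps users challenge their patterns | Self-monitoring |
| Control lacks the active features | Methods/design | Diary that supplies alternative thoughts, then hands over to the crisis module | Constantly monitored aspects |

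The left-hand claims and the right-hand content cannot both stand. Supplying an alternative thought at the moment of temptation is what the Theoretical framework section describes as CBT's aim. The contradiction holds whatever is decided about SIGMAi.

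**Step 2. Can controls reach SIGMAi?**

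1. SIGMAi is a sub-module of the gamified module (The gamified intervention module).
2. Controls do not get the gamified module (The SIGMA randomized controlled trial). From 1 and 2, controls do not get SIGMAi.
3. Controls keep the crisis module (same section).
4. The crisis module gives access to SIGMAi (Distraction). From 3 and 4, controls do get SIGMAi.

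The two conclusions conflict. Calling the control app modified makes the first more likely, but no sentence says that the link is removed. The diary's hand-over to the crisis module gives controls a second path to the same point. This is an unreconciled conflict; it does not show that controls have access.

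**Step 3. Which outcomes are affected?**

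- Belief and eating questionnaires: the shared tips and diary narrow the contrast in belief-related content. This is certain from the text, but its extent is unknown.
- Attention bias: affected only if the route in Step 2 is open.

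**Step 4. Can the effect be sized?** That would need the share of the active effect that reaches controls, and the documents give none. The Data analysis section also ties d = 0.50 to the trial as designed, that is, to SIGMA against this control. Discounting that figure for content both arms were always meant to share could count the same thing twice. No loss of power is therefore claimed.

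**The case against.** The strongest reply is that the comparison is disclosed. Methods/design states the primary objective as SIGMA against a sham with every module except the gamified one. That is a legitimate add-on contrast, and shared content does not bias it. Keeping the other modules also preserves the resemblance on which participant blinding relies. This stands, and it is why the control need not be stripped. It does not rescue the claim that the control leaves the mechanism untouched.

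A second reply is that the Distraction section describes the full SIGMA app, that excluding the gamified module ordinarily excludes SIGMAi, and that per-arm settings belong in the full protocol. This stands in part. A reader might infer that controls will be exposed to SIGMAi, but the documents do not establish that. They contain two statements that conflict and none that settles the matter.

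A reader might also infer that blinding is broken, because "the results of the game can also be shared on social media and with other users" and electronic recruitment posters are distributed "with a special focus on weight-related forums, Facebook groups, and websites". The documents do not support that as a finding. Sharing is optional, recruitment is spread across many channels nationally, and no statement shows that controls will see others' results or recognise what they imply about their own arm. It is a secondary, unproven risk. Such unblinding would probably favour SIGMA, whereas exposure of controls to active content pulls toward the null, so the net direction is unknown.

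**Conclusion.** The concern holds in a limited form. The description of the control as not addressing the mechanism of change is contradicted by the coping strategies and ABC diary that controls keep. That is wrong as written and rests on the protocol's own account of the mechanism, with no outside assumption. The status of the crisis-module route to SIGMAi is unresolved. Contamination of the attention-bias outcome depends on that route being open in the control build.

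The size of any dilution cannot be derived. A reader might be tempted to turn an assumed share of the effect into a fall in power, but any such share would be invented. What changes is the interpretation: the trial can estimate what the gamified module adds to an app with CBT tips and an ABC diary. It cannot, from a null result, give evidence against the CBT mechanism.

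**What to change.** 1. Reconcile the sections on the gamified intervention module, Distraction and the SIGMA randomized controlled trial by stating that the crisis-module link to SIGMAi is disabled in the control build. If builds with the link active are already in use, say so and report SIGMAi use among controls from the app log.
2. Drop the statements that the control does not address the mechanisms of change and lacks the active features. Describe it as the SIGMA app without the gamified module, retaining CBT-based tips and the ABC diary.
3. Restate the primary aim as the added effect of the gamified module over that app, and say in advance that a null result will not be read as evidence against the CBT mechanism.
4. List which crisis, diary and sharing functions are active in each arm. Naming the sharing functions is enough; the unproven unblinding risk does not by itself justify altering the SIGMA arm.

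The cost is one app setting and a few sentences. The downside is a narrower claim. The control keeps its messages, breathing tool and diary, so the resemblance between the two apps is otherwise unchanged.
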